## 1. INTRODUCTION AND RATIONALE

The evidence for the adverse effects of overweight on women's reproductive health is indisputable. Overweight affects reproductive capacity in all subfertile couples. Moreover, overweight is associated with pregnancy complications and poor neonatal outcome. Pregnancy complications associated with obesity are hypertensive disorders, gestational diabetes, prolonged duration of labour, increased need of operative delivery, macrosomia, shoulder dystocia and increased blood loss (Garbacia et al., 1985; Edwards et al., 1996). Obesity is associated with an increased risk of adverse pregnancy outcomes such as unexplained still birth (Cnattingius et al., 1998; Kristensen et al., 2005; Bergstrom et al., 1998; Linne et al., 2004), neonatal admissions (Usha Kiran et al., 2005) and five times higher costs (Linne et al., 2004).

Each year about 15.000 to 20.000 new couples present themselves with subfertility. In a large Dutch cohort study of 3.000 subfertile couples (Van der Steeg et al., 2007), 19% of the women had a BMI between 25 and 30, 7% had a BMI between 30 and 35, and 4% above 35. Thus, approximately 30% of these couples are overweight or obese.

Obesity has further been associated with reduced fertility in the general population (Ramlau-Hansen et al., 2007). Ovulatory subfertile women with a BMI of 29 kg/m^2 or higher have a 4% lower pregnancy rate per kg/m^2 increase (Van der Steeg et al., 2007). Obese women also have a lower live birth rate after IVF and ICSI (Norman et al., 1998; Wang et al., 2000; Wang et al., 2002; Fedorcsak et al., 2004; Lintsen et al., 2005).

The relationship between BMI and the risk of spontaneous abortion is inconsistent (Lashen et al., 1999; Fedorczak et al., 2000; Wittemer et al., 2000; Wang et al., 2001, Lintsen et al., 2005). A meta-analysis on the effect of overweight and obesity on ART reported a lower chance of pregnancy following IVF (OR 0.71, 95% CI: 0.620-0.81) and an increased miscarriage rate (OR 1.3, 95% CI: 1.06-1.68). Extrapolating from available data one could argue that the combination of lower chance of pregnancy and higher miscarriage rate in overweight and obese women could result in a reduced live birth rate (Maheshwari et al., 2007).

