### 4.2 Study design

The study is a multicenter randomized clinical trial. Subfertile women (age 18-39) with a BMI of 29 kg/m^2 or above will be included. Exclusion criteria are: azoospermia or donor semen, severe endometriosis, chronic anovulation due to WHO III and endocrinopathies. Women with an untreated pre-existent hypertension or diabetes type 1, or pregnancy-induced hypertension, preeclampsia, eclampsia or HELLP syndrome in a previous pregnancy are excluded.

The intervention consists of a structured lifestyle program of six months, which aims at realistic weight loss of at least 5% to 10%, achieved by the combination of a healthy diet (caloric reduction of 600kCal/day), increase of physical activity (aiming at 10.000 steps per day) and two to three times a week sporting activity, and behavioral modification. The structured lifestyle program, in which practice variation is minimized using a structured software program, has been developed, used and evaluated previously (Zon-MW project 50-

50110-98-078; the Groninger Overweight And Lifestyle study (GOAL)). After six months of lifestyle intervention patients will start fertility treatment as indicated.

In the “usual care” arm fertility treatment will be started if this is justified by the individual prognosis (guideline NVOG)

All randomized women will fill in questionnaires concerning: diet, eating behavior, physical activity and smoking: SF-36, FFQ, DEBQ, Squash list, at inclusion, and at 12 weeks, 6 months, 12 months and 24 months after randomization. Blood samples (10 cc) will be taken at the start, 3 months and 6 months after the start of the study.

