## 6.5 Study participants characteristics

Baseline characteristics include female age, ethnicity, education, current smoking, parity, duration and type of subfertility (anovulation, tubal factor, male factor, unexplained, other), biometrics (BMI, waist circumference, waist/hip ratio, systolic and diastolic blood pressure), partner characteristics (age, BMI, current smoker), fertility characteristics (ovulation/anovulation, PCO yes/no, sperm analysis results according to WHO standards, tubal patency), and Hunault prognostic index.

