Exploratory subgroup analyses of the primary outcome and ongoing pregnancy rates will be performed for spontaneous and treatment-induced pregnancies and for women with a BMI below 35 versus above 35, as well as for anovulatory versus ovulatory women and for women with a waist-hip ratio of above 0.8 versus below or equal to 0.8 and for women who are 36 years or older versus younger than 36 years based on tests of interaction with treatment group. The results of these analyses will be presented in a separate manuscript.

Additional analysis concerning the influence of HOMA, androgens, adipokines and cytokines on pregnancy chances and recovery of ovulations in anovulatory patients will be assessed using multivariate Cox-regression. The results of these analyses will be presented in a separate manuscript.

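### The exploratory interaction tests use cut versions of age, waist-hip ratio and BMI; testing the recorded values would keep information that the cuts discard, most clearly for age

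*Supplement*

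**What the plan says.** SAP 6.6 states: "Exploratory subgroup analyses of the primary outcome and ongoing pregnancy rates will be performed". Among the subgroups are a split of BMI, "for women with a BMI below 35 versus above 35", and splits of waist-hip ratio and age: "for women with a waist-hip ratio of above 0.8 versus below or equal to 0.8 and for women who are 36 years or older" are compared with those "versus younger than 36 years based on tests of interaction with treatment group". The results go to a separate manuscript. Protocol 8.2 (latest version) lists the same cuts for the primary outcome.

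SAP 6.5 shows that the underlying values are collected: "Baseline characteristics include female age, ethnicity, education, current smoking, parity" and, further on, "biometrics (BMI, waist circumference, waist/hip ratio, systolic and diastolic blood pressure". SAP 4.2 gives the eligible range: "Subfertile women (age 18-39", with BMI of 29 or above.

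The documents give no reason for 0.8 or 36, no distribution of age or waist-hip ratio, and no expected subgroup sizes. BMI 35 at least matches the British Fertility Society advice cited in SAP 4.1. No interaction test on the recorded values is planned.

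**The concern.** Cutting a continuous modifier treats all women on one side of the line as alike. If benefit changes gradually with age or fat distribution, the split discards the variation within each group, and the interaction test loses power. The loss grows as the split becomes more uneven. Age 36 sits near the top of the eligible range, so the older group is probably small.

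At stake is how the separate manuscript will be read. A non-significant interaction may be taken to mean that benefit does not vary with age or body-fat distribution, when the test was less sensitive than the collected data allowed. The primary comparison is not involved.

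**Working it through.** **The plan's own figure.** The plan gives no number for the subgroup tests, so the only figure to reproduce is the sample size that they inherit. Protocol 4.4 and SAP 6.1 assume 45% v 60%, 20% drop-out in the lifestyle arm, alpha 0.05 (two-sided, protocol summary) and 80% power.
- Diluted lifestyle rate, if drop-outs have the usual-care rate: 0.8 × 0.60 + 0.2 × 0.45 = 0.57.
- n per group = [1.96 √(2 × 0.51 × 0.49) + 0.842 √(0.45 × 0.55 + 0.57 × 0.43)]² / 0.12² = 271.2, rounded up to 272, as stated.
- Allowance for 5% loss: 272 × 1.05 = 285.6; the plan uses 285 per group, 570 in total.

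**Information kept by a split.** Suppose the interaction is linear in the modifier. The information kept by a two-group split, relative to the recorded value, is the squared correlation between the value and its group indicator. With p the share in the smaller group, z the normal cut-point and φ the normal density:
- normal modifier: φ(z)² / [p(1 − p)]
- uniform modifier: 3p(1 − p)

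**Power after the split.** Take an interaction that has 80% power on the recorded values, so its noncentrality is 1.96 + 0.84 = 2.80. After the split, power is Φ(2.80 × √kept − 1.96). For a normal modifier:

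| Smaller group | Information kept | Lost | Power after split |
|---|---|---|---|
| 50% | 0.637 | 36% | 61% |
| 30% | 0.576 | 42% | 57% |
| 20% | 0.490 | 51% | 50% |
| 15% | 0.426 | 57% | 45% |
| 10% | 0.342 | 66% | 37% |

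The loss reaches half when the smaller group is about 21% (0.209 normal, 0.211 uniform). A logistic simulation with 570 women and 2,000 runs per split, started at about 80% power on the continuous scale, gave 62%, 57%, 48%, 45% and 37% for the same five splits.

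**Age at 36 (distribution assumed; the documents give none).**
- Uniform from 18 to 39: share = 3/21 = 14%; kept 3 × 0.143 × 0.857 = 0.37; 63% lost.
- Uniform up to the 40th birthday: share = 4/22 = 18%; kept 0.45; 55% lost.
- Normal truncated to the eligible range, mean 28-32, SD 4-5: share 2-17%; kept 0.12-0.40; 60-88% lost.
- At an assumed mean of 34 the share is about 26% and the loss about half.

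Across means 28-32 and the uniform cases, the older group holds about 12 to 104 of 570 women (0.021 × 570 to 0.182 × 570), and power after the split is about 17-46% where the recorded values would give 80%.

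**Waist-hip ratio at 0.8 (assumed normal, mean 0.80-0.90, SD 0.06-0.08).** The share at or below 0.8 runs from 5% to 50%, and information kept from 0.22 to 0.64, so 36-78% is lost. The loss was under half in 7 of the 12 combinations tried. Power after the split is about 26-61%.

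**How much power there is to lose.** Consider an interaction as large as the whole 15-point design effect, with variance 0.25 per woman.
- Even split: SE = √(0.25 × 4/142.5) = 0.0838; 0.15/0.0838 = 1.79; power 43%.
- The same gradient on the recorded scale: 1.79/√0.637 = 2.24; power 61%.
- At half that size: about 14% with the split and 20% without.
- With the full 15 points between groups but uneven splits: 30% at 20/80 and 19% at 10/90.

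**The case against.** **Exploratory status and low power.** The analyses are labelled exploratory, the cuts are pre-specified, the criterion is an interaction test rather than separate within-group p-values, and no decision depends on the result. Two-group displays are a common way to show subgroups. All of this stands, and it makes the point minor. It also follows that a null interaction cannot be blamed mainly on the cut: for interactions of plausible size, power is low on either scale.

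**The linearity assumption.** The information losses hold for a smooth, roughly linear interaction. If the effect were a true step at 36 or 0.8, the split would lose less or even do better. This stands as a condition. Protocol section 1 says that ovulatory women from BMI 29 upwards "have a 4% lower pregnancy rate per" unit of BMI. A reader might take this as evidence of a gradient in the programme's benefit, but it concerns BMI and prognosis. It does not show that benefit changes with BMI, and it says nothing about age or waist-hip ratio. No passage supports a step either.

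**Waist-hip ratio.** A reader might infer that both cuts leave small subgroups and lose half the information or more. The documents do not support that for waist-hip ratio. They give no distribution, and if the mean were near 0.80 the groups would be equal and the loss about 36%.

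**Conclusion.** The point holds as a minor, inexpensive improvement. All three modifiers are measured as continuous values but tested only as two groups, and 0.8 and 36 are unexplained.

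For a linear interaction and a normally distributed modifier, the split loses at least about a third of the information, and about half or more once the smaller group is about a fifth or less. For age, a loss of more than half appeared under uniform ages and every assumed mean from 28 to 32; it comes down to about half only with a mean near 34. For waist-hip ratio the direction is the same, but the size cannot be fixed within 36-78%. The documents give no basis for a figure for BMI at 35, although the same reasoning applies.

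These sizes rest on assumed distributions and a linear shape. The primary intention-to-treat comparison and the sample size are unaffected.

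**What to change.** In SAP 6.6, state that interaction of treatment with age, waist-hip ratio and BMI will be tested with the modifier continuous (linear term, with a spline check of shape) in the regression model used for the outcome, and that the estimated treatment effect will be shown across the modifier's range. The sentence should name that model, since the subgroup paragraph does not; SAP 6.6 already plans Cox regression for delivery rates over time. Keep the 36, 0.8 and 35 groups for descriptive display, with the number of women in each. Protocol 8.2 should match.

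The cost is a sentence or two and no new data. The downside is that the test assumes a smooth shape and would gain less, or lose, if the effect were a real step at the cut; the spline check and the grouped display help to show that. Because power stays low under either method, the report should give interaction estimates with confidence intervals and should not read a non-significant test as absence of variation.

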#### 6.7 Lifestyle program effectiveness

The effects of the lifestyle program will be presented as the changes in body weight, BMI, systolic and diastolic blood pressure, waist circumference and waist/hip ratio for both groups, presented as mean or median with standard deviation or interquartile range as appropriate from randomization until the occurrence of a pregnancy. In addition, the change in percentage of ovulatory women will be compared between the groups. The results of these analyses will be presented in a separate manuscript.

